### Data analysis

2.8

Data will be collected using a standardized data entry form and entered into the data management system. The intention-to-treat principle will be used for data analysis. Participant characteristics will be described using means and standard deviations for continuous data and frequencies and percentages for categorical data. The 3 groups will be compared using an analysis of variance (ANOVA) or the nonparametric equivalence Kruskal–Wallis test if required. To compare paired data (intragroup) between 2 different points, we will use repeated-measures ANOVA and Friedman tests for continuous and nonparametric data, respectively. Statistical significance will be defined as a *P* value < .05. All statistical analyses will be performed using SPSS version 19.0 for Windows (IBM Corp, Chicago, IL).

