### Objectives

1.2

We aim to develop a critical pathway for FIRM and compare the effectiveness of this program with those of conventional postoperative rehabilitation and historical control treatment for individuals after hip fracture surgery. We also propose to delineate the feasibility of applying FIRM in a chronic-care or community-based hospital setting.

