### Sample size

2.3

According to the preliminary and unpublished data of a pilot study, the mean difference and standard deviation of Koval walking ability (as a primary outcome) were 1.034 and 1.075, respectively. To detect a mean difference in the Koval walking ability grade of 0.5 for the FIRM group (0 for the conventional group and −0.5 for the control group) with at least 80% power and a significance level of 0.05 using a 2-tailed test, each group must include 85 patients (255 in total). To allow for 10% attrition, our aim is to recruit 94 patients per group (282 in total). PASS version 14.0 (NCSS, Kaysville, UT) was used to calculate the required sample size.

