#### Control group

2.6.3

This group will consist of an age- and sex-matched historically controlled cohort. Participants will be discharged without having received PT during the postoperative hospitalization period. The aim will be to determine the natural course of the patients’ functional status.

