### Outcome measures

2.7

The following demographic data will be collected at baseline: age, sex, fracture location and laterality, type of surgery, and underlying disease. Functional outcomes will be measured at 1 (before intervention) and 3 weeks (after 2 weeks’ intervention), 3, 6, and 12 months after operations.

The primary outcome of this study will be Koval walking ability scores^[11]^ (range: 1–7; with a higher score indicating a worse outcome), which rates physical functioning according to walking dependency. The secondary outcomes will be as follows: physical functioning and walking ability, assessed according to the functional ambulatory category^[12]^ (range: 0–5; a lower score indicates a worse outcome) and the modified Rivermead mobility index^[13]^ (range: 0–40; a lower score indicates a worse outcome); balance and fall risk, assessed using the Berg balance scale^[14]^ (range: 0–56; a lower score indicates a worse outcome); cognition, evaluated using the Korean version of the Mini-Mental State Examination^[15]^ (range: 0–30; a lower score indicates a worse outcome); mood, evaluated using the Korean version of the Geriatric Depression Scale^[16]^ (range: 0–30; a lower score indicates a worse outcome); quality of life (QOL), evaluated using the Euro Quality of Life Questionnaire 5-dimensional classification^[17]^ (EQ-5D; range: 0–1; a lower score indicates a worse outcome); ADLs determined using the Korean version of the modified Barthel index^[18]^ (range: 0–100; a lower score indicates a worse outcome) and the Korean version of the Instrumental ADL^[19]^ (range: 0–3; a higher score indicates a worse outcome); and frailty assessed based on fatigue, resistance, ambulation, illnesses, and loss of weight (FRAIL) using the Korean version of the FRAIL scale^[20]^ (K-FRAIL; range: 0–5; a lower score indicates a worse outcome). Functional assessments will be conducted with the control group via telephone surveys performed at the same time points but measures will be limited to the Koval and EQ-5D. The adherence and drop-out rates of the program will be monitored during stage 2, in which FIRM will be applied in the community-based hospital system. Each researcher charged with outcome evaluation at each of the 3 core hospitals will work on standardizing all measuring protocols by arranging a consensus meeting before the start of the study. Regular meetings to discuss ways to unify the measurement methods will then be held.

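### The only between-group test named for Koval is a three-group omnibus test that includes the historical control, so it does not isolate FIRM versus conventional rehabilitation and does not match the sample size

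*Protocol article*

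**What the plan says.** The objective in section 1.2 is to "compare the effectiveness of this program with those of conventional postoperative rehabilitation and historical control treatment". That is two comparisons, each with FIRM on one side.

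Section 2.8 gives the between-group analysis in one sentence: "The 3 groups will be compared using an analysis of variance (ANOVA) or the nonparametric equivalence Kruskal–Wallis test if required". The only other inferential methods there are for change within a group: "To compare paired data (intragroup) between 2 different points, we will use repeated-measures ANOVA and Friedman tests". The significance threshold is P < .05. The section names no contrast between two specific arms.

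On the third group, section 2.6.3 states: "This group will consist of an age- and sex-matched historically controlled cohort". Section 2.7 has it assessed by telephone, and "measures will be limited to the Koval and EQ-5D". Koval is the primary outcome, so this group is part of the three-group test on it.

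Section 2.3 reports pilot figures ("the mean difference and standard deviation of Koval walking ability (as a primary outcome) were 1.034 and 1.075, respectively") and plans for 0.5 in the FIRM group, with "0 for the conventional group and −0.5 for the control group". It arrives at 85 per group, or 94 after attrition, for at least 80% power with a two-tailed test at 0.05.

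**The concern.** An omnibus test rejects when any of the three means departs from the others. It has no direction and does not say which group is responsible. Here the plan itself expects the control group to do worse than the conventional group by half a grade. That gap alone can produce a significant result even if the added FIRM components do nothing beyond conventional rehabilitation.

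The control group is described as historical, receives no physical therapy in hospital and is assessed by telephone. It is therefore the group whose difference is hardest to attribute to treatment. If the one named test is significant and is read as showing that FIRM works, the conclusion may rest wholly on that group. The Discussion looks ahead to nationwide use of FIRM, so the distinction matters in practice.

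**Working it through.** **Inputs.** From section 2.3: means 0.5 / 0 / −0.5 for FIRM / conventional / control, SD 1.075 (variance 1.155625), 85 evaluable per group, 94 recruited, two-sided 0.05. Two assumptions are mine. I read 0.5 / 0 / −0.5 as amounts of improvement, because a higher Koval grade is worse; reversing all the signs changes nothing below. I use the normal-theory F test in place of Kruskal–Wallis, and return to this in step 3.

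**1. Which test does 85 per group fit?**

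Omnibus F: noncentrality λ = n × Σ(mean − grand mean)² / variance, with 2 and 3(n − 1) degrees of freedom. The planned means give Σ = 0.25 + 0 + 0.25 = 0.5.
- n = 23: λ = 9.95, power 79.4%.
- n = 24: λ = 24 × 0.5 / 1.155625 = 10.38, power 81.3%. So 24 per group suffice.
- n = 85: λ = 36.8, power 99.99%.

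Two-group t test, FIRM versus conventional: noncentrality = 0.5 / (1.075 × √(2/n)).
- n = 73: power 79.7%.
- n = 74: power 80.2%. So 74 per group are needed.
- n = 85: noncentrality 3.03, power 85.4%.
- n = 94: noncentrality 3.19, power 88.7%.

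Neither calculation returns exactly 85. Undeclared pairwise variants come close: allowing for a rank test gives 74 / 0.864 = 85.6, and a Dunnett-type adjustment gives 87. I do not call 85 wrong, since it meets the stated power for the plain pairwise contrast. It is more than three times what the named ANOVA needs.

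**2. How often is the named test significant when FIRM adds nothing over conventional?**

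Set the means to 0 / 0 / −0.5. The grand mean is −1/6 and Σ = 1/36 + 1/36 + 4/36 = 1/6.
- n = 85: λ = 85 × (1/6) / 1.155625 = 12.26; critical F(2, 252) = 3.03; P < .05 in 88.6% of trials.
- n = 94: 91.7%.

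The result depends on the control gap (n = 85):

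| Control worse by | Omnibus significant |
|---|---|
| 0.25 (Σ = 1/24, λ = 3.06) | 32% |
| 0.5 | 89% |
| 0.75 | 99.8% |

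If FIRM is 0.25 worse than conventional and control 0.5 worse than conventional (Σ = 0.125, λ = 9.19), the test is still significant in 77% of trials.

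**3. How often is it significant while FIRM versus conventional is not?**

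By simulation with means 0 / 0 / −0.5 and n = 85, the omnibus test and the FIRM–conventional t test are both significant in about 5.0% of trials. That leaves 88.6 − 5.0 = 83.6%, about 84%. Separately, Kruskal–Wallis on data rounded to a 1–7 scale (assumed centres 4, 4 and 4.5) is significant in about 84% of trials against 88.6% for the F test in step 2. The rank alternative does not remove the problem.

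**4. Do follow-up pairwise tests inflate type I error?**

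With three groups and pairwise tests run only after a significant omnibus test, simulated familywise error is about 5% under the global null. With means 0 / 0 / −0.5, the FIRM–conventional contrast is falsely significant in about 5% of trials, of which about 2.5% favour FIRM. Three pairwise tests with no omnibus gate give about 12%.

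**The case against.** **No success rule.** The article nowhere says that the trial succeeds if the omnibus P value is below .05. This stands. The 89% and 84% figures describe the only criterion it states, not a declared decision rule.

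**Detail left to another document.** Pairwise follow-up may be set out in a statistical analysis plan that is not shown. That is possible, so the absence of a testing order or an alpha split is no finding. But section 2.8 does name a between-group test, and that test conflicts with the objective in section 1.2 and the size in section 2.3. That mismatch is in the text.

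**Type I error.** A reader might infer that unadjusted pairwise tests would inflate familywise error to about 12%. The document does not support this. The figure applies only to ungated tests, whereas the plan starts from an omnibus test, and with three groups gating holds the error near 5%.

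**Pairwise intent.** The two-tailed wording and the size of 85 suggest that the authors had a pairwise contrast in mind. I agree. It shows that section 2.8 should say so.

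**Secondary outcomes.** A reader might infer that the between-group analysis fails for most secondary outcomes. For these only FIRM and conventional have data, and ANOVA or Kruskal–Wallis on two groups is the comparison wanted. The point therefore bites on Koval and EQ-5D; elsewhere the three-group wording only needs correcting.

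**Status of the control group.** The abstract and section 2.5 speak of randomisation to all three groups, while sections 1.2, 2.1.1 and 2.6.3 call the control historical. That contradiction is a separate matter. Even with a randomised control, the omnibus test would not isolate FIRM versus conventional.

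**Conclusion.** The point holds for the primary outcome. The one between-group test named for Koval does not answer either comparison in the objective, and it is not the test that 85 per group suits (24 would do for it, against 74 for the FIRM–conventional contrast).

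If FIRM equals conventional and control is worse by the plan's own 0.5, the named test is significant in about 89% of trials, and in about 84% it is significant with no significant FIRM–conventional difference. These figures rest on SD 1.075, 85 per group, normal theory and a 0.5 control gap; at a gap of 0.25 the 89% falls to about 32%. They measure how weakly a significant omnibus result speaks to FIRM versus conventional. They are not a type I error rate for that contrast.

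**What to change.** In section 2.8, replace the three-group sentence with text to this effect: the primary analysis compares Koval between FIRM and conventional among randomised patients at two-sided 0.05; comparisons with the historical control, on Koval and EQ-5D only, are secondary and are tested after the primary contrast; all other secondary outcomes are compared between FIRM and conventional only, because the control group has no data on them. Koval is measured at five time points, so the sentence should also carry whichever one the full protocol designates as primary.

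The cost is wording. No patients need to be added: the contrast has 85% power at 85 per group and 89% at 94 for the stated difference of 0.5. The one small downside is that section 1.2 lists the two comparators without ranking them, and this change makes the historical-control comparison secondary.

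### The between-group rule leaves two unadjusted tests open for Koval, a 7-grade ordinal primary outcome, and neither uses the week-1 grade; fix one baseline-adjusted ordinal analysis

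*Protocol article*

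**What the plan says.** Protocol article, section 2.8 (Data analysis), has one between-group rule for all outcomes: the three groups are compared by ANOVA "or the nonparametric equivalence Kruskal–Wallis test if required". It gives no trigger for the switch and does not say which test applies to Koval. For within-group comparisons over time the same section says "we will use repeated-measures ANOVA and Friedman tests for continuous and nonparametric data, respectively".

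Section 2.7 (Outcome measures) makes Koval the primary outcome ("range: 1–7; with a higher score indicating a worse outcome"). It is measured at week 1, before the intervention, and again at 3 weeks and at 3, 6 and 12 months.

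Section 2.3 (Sample size) treats Koval as a mean: in the pilot, "the mean difference and standard deviation of Koval walking ability (as a primary outcome) were 1.034 and 1.075, respectively". The aim is to "detect a mean difference in the Koval walking ability grade of 0.5 for the FIRM group", "with at least 80% power and a significance level of 0.05 using a 2-tailed test", with 85 patients per group before attrition.

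**The concern.** Three sections point different ways on how Koval is to be analysed. The sample size implies a comparison of means, the scale implies an ordinal or rank method, and the analysis section allows either on an unstated condition. The tests address different hypotheses (equal means, or equal rank order) and can disagree on borderline data. If the choice is left to judgement after the data are in, the primary P value depends on it.

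The second weakness lies in both branches of the rule. One-way ANOVA and Kruskal–Wallis compare follow-up grades without regard to where each patient stood at week 1, and neither takes account of hospital. The repeated-measures tests do use week 1, but the article assigns them to change within a group, so they do not adjust the comparison between groups. Kruskal–Wallis also gives no effect estimate for FIRM against conventional care. At stake are power and a usable estimate more than validity.

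**Working it through.** **Inputs from section 2.3.** Difference 0.5 grade, SD 1.075, two-sided 5%, 85 per group. The documents give no Koval distribution and no correlation between week 1 and follow-up, so the shapes and correlations below are assumptions.

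**The plan's own figure.** For two groups, n = 2(1.96 + 0.842)² × 1.075² / 0.5² = 72.6, so 73 per group (74 with the t distribution). The stated 85 is not reproduced from these inputs. That is a separate matter; 85 is used below because it is the planned size.

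**Step 1: cost of the open choice.** Scores on seven grades were simulated for three groups of 85, with 20,000 null trials per shape (Monte Carlo standard error √(0.05 × 0.95 / 20,000) = 0.15 points) and 4,000 trials with one group shifted by 0.5 grade through a proportional-odds shift.

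| Assumed shape (SD) | Type I: ANOVA | Type I: Kruskal–Wallis | Type I: smaller P | Power: ANOVA | Power: Kruskal–Wallis |
|---|---|---|---|---|---|
| Symmetric (1.08) | 5.1% | 5.1% | 6.0% | 89.8% | 90.5% |
| Skewed (1.34) | 4.9% | 5.1% | 6.6% | 78.5% | 86.3% |
| Skewed (1.87) | 5.0% | 4.9% | 5.7% | 44.7% | 46.6% |
| U-shaped (2.44) | 5.0% | 4.9% | 5.5% | 25.7% | 26.2% |
| Piled at worst grades (1.51) | 4.9% | 4.8% | 6.5% | 55.5% | 59.2% |

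- Each test fixed in advance holds about 5%.
- A switch triggered by Shapiro–Wilk gave the same results as Kruskal–Wallis for every shape, because that test rejected normality in essentially every data set.
- Inflation appears only when the smaller P value is taken: 5.5–6.6% here. Two further sets of assumed shapes gave 5.7–6.8% and 4.8–6.9%.
- Kruskal–Wallis gains about 0 to 8 points of power over ANOVA, depending on shape.
- In a separate 500-trial set, an unadjusted proportional-odds test was within about 1.5 points of Kruskal–Wallis.

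**Step 2: cost of ignoring week-1 Koval.** Two groups of 85 were simulated with ordinal scores and an assumed latent correlation between week 1 and follow-up. Type I error of the adjusted analysis stayed near 5%. The gain in power over the unadjusted tests was:

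| Latent correlation | Gain in power |
|---|---|
| 0.3 | about 1–4 points |
| 0.5 | about 8–11 points |
| 0.7 | about 18–21 points |

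**Cross-check by formula on the mean scale.** Power = Φ(0.5 / [1.075 √(1 − ρ²) √(2/85)] − 1.96).

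- ρ = 0: 0.5 / 0.1649 = 3.03, power 85.8%.
- ρ = 0.3: 0.5 / 0.1573 = 3.18, power 88.9% (+3).
- ρ = 0.5: 0.5 / 0.1428 = 3.50, power 93.8% (+8).
- ρ = 0.7: 0.5 / 0.1178 = 4.25, power 98.9% (+13).

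The last gain is below 18–21 points because a start at 85.8% leaves little room. From 75% unadjusted power the same formula gives 95.8% at ρ = 0.7 (+21). The cross-check takes 1.075 as the SD of the follow-up grade. Section 2.3 does not say whether it is that or the SD of a change.

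**The case against.** The strongest reply is that the switch does no harm. If a normality check drives it, Koval will nearly always fail, the analysis will be Kruskal–Wallis, and that is in effect a fixed test at the right level. The next sentence of section 2.8 sorts tests by type of data. Read the same way, the between-group rule would send Koval to Kruskal–Wallis before any data are seen. The article is also condensed, the full plan may name the test, and the statistician is to work with nominal group names. An odds ratio fits less directly with a sample size built on a mean difference, and it brings its own assumption.

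Much of this stands. A reader might infer that the clause by itself breaks the 5% level; it does not, since inflation needs a choice made after both P values are known. A reader might infer that any normality check must reject a 7-grade score. The article names no check, and for the symmetric shape a skewness-and-kurtosis test (D'Agostino) rejected in only 3.2% of data sets. A reader might also infer that fixing an ordinal test gains power over Kruskal–Wallis; without baseline adjustment the two are practically equal.

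What does not stand is that nothing needs changing. The article is not silent: it states a rule, and nothing in it assigns Koval to either branch. Nominal group names do not hide P values, and the control group can be recognised because only Koval and EQ-5D are collected for it. On the most favourable reading, the result is still an unadjusted rank test with no estimate of effect, although week-1 Koval is collected.

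**Conclusion.** The point holds in limited form. Two unadjusted tests are left open for an outcome whose ordinal scale is known in advance, and neither uses the baseline grade. The open choice is a modest fault: no inflation if it always lands on one test, and about 5.5–7% type I error if the test is picked after seeing both P values. The larger gain comes from baseline adjustment, about 1 to 21 points of power at 85 per group for latent correlations of 0.3 to 0.7. All these figures rest on assumed Koval distributions and correlations, and the gain is small if week-1 grade predicts later grade poorly, as it might if most patients share the same grade one week after surgery. The article does not support a claim that the planned tests are invalid. The change is worth making because it is cheap and gives the trial an effect estimate.

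**What to change.** In section 2.8, take Koval out of the general rule, drop the conditional clause for it, and state:

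- One primary between-group analysis that does not depend on the observed distribution: a proportional-odds (cumulative logit) model with group, week-1 Koval and hospital, applied at the follow-up time that the sponsor names as primary.
- The headline result is the FIRM-versus-conventional common odds ratio with 95% CI. Its direction must be stated, since a higher grade is worse.
- The mean grade difference and the distribution of grades by group are shown beside it. The first keeps the link to section 2.3; the second lets a reader judge the proportional-odds assumption.
- Kruskal–Wallis is a sensitivity analysis.

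A sentence in section 2.3 should confirm that 85 per group suffices under this analysis. No extra data or patients are needed: week-1 Koval and hospital are already recorded. The cost is about one paragraph plus that confirmation. The small downside is that an odds ratio is less direct than a difference in grades and rests on proportional odds. If the full analysis plan already fixes such an analysis, the article's wording need only be brought into line with it.

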### Recruitment

2.4

For the comparative clinical trial, all patients will be enrolled in 3 core hospitals. On the second day after hip fracture surgery, patients who meet the inclusion but not the exclusion criteria will be preliminarily screened by researchers in cooperation with orthopedic surgeons. Patients who agree to participate in the study will be finally enrolled. In a test of this protocol, the ratio of patient enrolments among Seoul National University Bundang Hospital, Chung-Ang University Hospital, and Jeju National University Hospital was 5:3:2 compared to the average number of hip fracture surgeries at the 3 hospitals. In stage 2, all participants will be enrolled consecutively.

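### The between-group Koval test names no baseline or hospital adjustment, and change over time is tested only within groups, which does not compare FIRM with conventional care

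*Protocol article*

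**What the plan says.** Outcome measures (2.7) sets the primary outcome: "The primary outcome of this study will be Koval walking ability scores". The scale runs from 1 to 7, higher being worse. On timing it says "Functional outcomes will be measured at 1 (before intervention) and 3 weeks", followed by visits at 3, 6 and 12 months. A pre-intervention Koval is therefore collected. For the control group, "Functional assessments will be conducted with the control group via telephone surveys performed at the same time points".

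Data analysis (2.8) has two sentences on inference. Between groups: "The 3 groups will be compared using an analysis of variance (ANOVA) or the nonparametric equivalence Kruskal–Wallis test if required". No covariate, no visit, and no choice between raw score and change is given. Over time: "To compare paired data (intragroup) between 2 different points, we will use repeated-measures ANOVA and Friedman tests". The same section states: "The intention-to-treat principle will be used for data analysis".

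Recruitment (2.4) describes enrolment at three core hospitals, where the ratio in a test of the protocol "was 5:3:2 compared to the average number of hip fracture surgeries at the 3 hospitals".

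**The concern.** Two features of the stated analysis fit poorly with the objective of comparing FIRM with conventional rehabilitation.

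First, the methods suited to repeated visits are assigned expressly to comparisons inside one group. Patients are followed from one week after hip surgery, when some recovery is expected in any arm; the article itself gives the control arm the purpose of showing the natural course. A significant change within the FIRM group cannot separate the programme from that recovery, and no between-group test of change or trajectory is named.

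Second, the between-group test carries no term for week-1 Koval or for hospital. If it is run as written on follow-up scores, a chance difference between arms in week-1 walking ability goes uncorrected, and variance that the baseline could explain stays in the error term. The first feature affects which question the P values answer; the second affects precision and protection against imbalance.

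**Working it through.** **Within-group change.** Write the expected change in an arm as R + T, where R is natural recovery and T the effect of that arm's rehabilitation.
- The within-FIRM test examines R + T(FIRM) = 0.
- The within-conventional test examines R + T(conv) = 0.
- The trial's question is T(FIRM) − T(conv) = 0. R cancels only when the two arms are contrasted directly.

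Whenever R is not zero, a within-group test can be significant with T(FIRM) = T(conv). This follows from the form of the test and needs no figures.

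**Inputs for the adjustment.**
- From Sample size (2.3): 85 per group, adjacent group difference 0.5, SD 1.075, two-sided 0.05, power of at least 80%.
- The section introduces the pilot figures thus: "the mean difference and standard deviation of Koval walking ability (as a primary outcome) were 1.034 and 1.075, respectively". It does not say whether 1.075 belongs to a raw score or to a change.
- The correlation r between week-1 and later Koval is not given. I assume 0.3 to 0.7.

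**The plan's own figure.** The plain two-group formula gives n = 2(1.960 + 0.842)² × 1.075² / 0.5² = 72.6, so 73 per group (74 by t-test). The stated 85 is reached if 73 is divided by 0.864, the minimum relative efficiency of a rank test: 73/0.864 = 84.5, so 85. The article does not name that allowance. I take 85 as given.

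**Unadjusted power at 85.** SE = 1.075 × √(2/85) = 0.165. Then 0.5/0.165 − 1.960 = 1.07, and power = 85.8% (85.4% by t-test). This exceeds the stated 80% for one pairwise comparison.

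**Adjusted power if 1.075 is the raw-score SD.** Residual SD = 1.075 × √(1 − r²).

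| r (assumed) | Residual variance, % of unadjusted | n per group for 80% | Power at 85 |
|---|---|---|---|
| 0 | 100 | 73 | 85.8% |
| 0.3 | 91 | 67 | 88.9% |
| 0.5 | 75 | 55 | 93.8% |
| 0.7 | 51 | 38 | 98.9% |

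The t-based powers at r = 0.3 and 0.5 are 88.5% and 93.6%.

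**Adjusted power if 1.075 is the SD of change.** With equal variances at the two visits, residual SD = 1.075 × √((1 + r)/2). An unadjusted comparison of change again has 85.8% power.

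| r (assumed) | n per group for 80% | Power at 85 |
|---|---|---|
| 0.3 | 48 | 96.4% |
| 0.5 | 55 | 93.8% |
| 0.7 | 62 | 90.8% |

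The pattern over r reverses, but under both readings adjustment gives more power than the unadjusted test. No size can be put on the hospital term, because the article gives no between-hospital variation.

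**The case against.** The strongest reply is that a between-group test is planned and stands immediately before the intragroup sentence. Nothing says that the within-group P values will support the efficacy claim. This stands: one cannot say that FIRM will be credited with natural recovery. What remains is that the only stated analysis of change cannot answer the trial's question.

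A second reply is that the baseline may already be in use. The sample-size pattern of 0.5, 0 and −0.5 cannot be raw scores on a 1–7 scale, and ANOVA on change scores is not excluded. This also stands, so it would be too strong to say that the plan ignores the week-1 value; it names no use of it. A change-score analysis is still less efficient than adjustment. With 1.075 as the raw-score SD, it needs 102, 73 or 44 per group for 80% power at r = 0.3, 0.5 or 0.7, against 67, 55 or 38 with adjustment.

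A reader might also infer that incomplete patients are dropped, against the intention-to-treat statement, because classical repeated-measures ANOVA and Friedman tests need all the values compared. The article does not say so. Its tests concern two points at a time, and missing-data rules may sit in an analysis plan that is not shown. The inference is a conditional risk, not a contradiction.

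Finally, a reader might treat the pilot's 1.034 and 1.075 as a within-patient change and derive a very large within-group t statistic. The article does not identify them as such, and the argument does not need that figure.

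**Conclusion.** The point holds in this form: the stated between-group test names no use of week-1 Koval or hospital, and the repeated-measures tests are confined to within-group comparisons, which do not test FIRM against conventional care. It should be changed, but it does not invalidate the trial.

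The documents do not support calling the plan underpowered on this ground, since about 85% at 85 per group meets the stated 80% for one pairwise comparison. Adjustment brings this to about 89% (r = 0.3) or 94% (r = 0.5) if 1.075 is a raw-score SD, or to about 96% down to 91% (r = 0.3 to 0.7) if it is the SD of change. Every r is assumed. If week-1 scores cluster at the worst grades, r would be low, and with 1.075 as a raw-score SD the gain would be small.

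Nor should a mixed model be read as a complete remedy. It retains partly observed patients validly only if data are missing at random. It does not by itself handle follow-up ended by death, and the article's background cites mortality of up to 36% within a year. It cannot make a historical control arm assessed by telephone comparable with the other two. It also needs a visit for the main contrast, which the article does not name.

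**What to change.** In Data analysis, make the Koval analysis a between-group comparison of FIRM with conventional care, adjusted for week-1 Koval and hospital. Either of two forms would serve:
- ANCOVA at one named follow-up visit; or
- a linear mixed model over the post-intervention visits with group, visit, group-by-visit, week-1 Koval and hospital, and the FIRM–conventional contrast at a named visit.

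Add an ordinal (for example proportional-odds) or rank-based sensitivity analysis, because the scale has only seven levels. Report within-group changes descriptively, without P values. If the mixed model is chosen, state its missing-at-random assumption and say separately how deaths are handled. Keep comparisons with the control group apart, since adjustment does not resolve its historical status or its mode of assessment. In Sample size, say whether 1.075 is the SD of a score or of a change.

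The cost is wording and programming. The week-1 Koval and the hospital are already recorded, and the named software has a mixed-model procedure. Neither data collection nor the sample size needs to change.
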